## Abstract

**Background:**

The success and cost-effectiveness of bowel cancer screening depends on achieving and maintaining high screening uptake rates. The involvement of GPs in screening has been found to improve patient compliance. Therefore, the endorsement of screening by GPs may increase uptake rates amongst non-responders.

**Methods/Design:**

A two-armed randomised controlled trial will evaluate the effectiveness of a GP endorsed reminder in improving patient participation in the NHS Bowel Cancer Screening Programme (NHSBCSP). Up to 30 general practices in the West Midlands with a screening uptake rate of less than 50% will be recruited and patients identified from the patient lists of these practices. Eligible patients will be those aged 60 to 74, who have previously been invited to participate in bowel screening but who have been recorded by the Midlands and North West Bowel Cancer Screening Hub as non-responders. Approximately 4,380 people will be randomised in equal numbers to either the intervention (GP letter and duplicate FOBt kit) or control (no additional contact) arms of the trial.

The primary outcome measure will be the difference in the uptake rate of FOBt screening for bowel cancer between the intervention and control groups at 13 weeks after the GP endorsed reminder and duplicate FOBt kit are sent. Secondary outcome measures will be subgroup analyses of uptake according to gender, age and deprivation quartile, and the validation of methods for collecting GP, NHSBCSP and patient costs associated with the intervention. Qualitative work (30 to 40 semi-structured interviews) will be undertaken with individuals in the intervention arm who return a FOBt kit, to investigate the relative importance of the duplicate FOBt kit, reminder to participate, and GP endorsement of that reminder in contributing to individuals' decisions to participate in screening.

**Discussion:**

Implementing feasible, acceptable and cost-effective strategies to improve screening uptake amongst non-responders to invitations to participate is fundamentally important for the success of screening programmes. If this feasibility study demonstrates a significant increase in uptake of FOBt screening in individuals receiving the intervention, a definitive, appropriately powered future trial will be designed.

**Trial registration number:**

ISRCTN: ISRCTN86784060

## Background

Colorectal cancer (CRC) is the third most common cancer, and second leading cause of cancer death in the UK, with 35,000 diagnoses and 16,000 deaths per year [1]. It incurs an annual expenditure of more than £300 million in surgical, adjuvant and palliative treatment [2] which could be significantly reduced by earlier diagnosis through bowel cancer screening. The five-year survival rate for CRC is currently around 47% [3], lower than in other European countries [4,5]. Despite improvements in cancer survival over the past decade, the deprivation gap in survival for many cancers, including CRC, has been widening [6], and a key recommendation of the Department of Health's 2011 Cancer Reform Strategy is the development and implementation of strategies to facilitate earlier diagnosis of cancer, including the improvement and expansion of screening [7].

Biennial bowel screening using the Faecal Occult Blood test (FOBt) has been shown in randomised controlled trials (RCTs) to have the potential to reduce mortality from bowel cancer by 16% [8]. FOBt screening in the average risk asymptomatic population can detect bowel cancer at an earlier stage than would be the case through symptomatic presentation, meaning that treatment is more likely to be effective [9]. In addition to improved survival, the benefits of earlier diagnosis through screening include improved patient quality of life and reduced NHS treatment costs [10]. However, if these benefits are to be realised, high levels of screening uptake and continued adherence over time must be achieved and maintained in the eligible population.

In England, bowel cancer screening using FOBt was introduced in 2006 and has now been rolled out nationally, co-ordinated through the NHS Bowel Cancer Screening Programme (NHSBCSP). The programme aims to screen men and women aged between 60 and 74 every two years, using a guaiac faecal occult blood test. Evaluations carried out when the programme was in the pilot stage demonstrated relatively low rates of uptake (58.5% and 52% in the first and second rounds of screening respectively) [11,12].

Interventions to increase uptake are required, and in particular, the development of feasible and acceptable strategies to improve compliance with bowel cancer screening amongst non-responders. Several studies have investigated the role of various interventions in increasing compliance with cancer screening [13]. Patient interventions have typically focused on the effectiveness of invitations to screening in increasing uptake [14]; reminders sent to those who fail to respond to invitations for screening [15], and educational interventions to increase knowledge about a given screening programme [16,17]. Interventions aimed at providers have focused on reminders or prompts to general practitioners (GPs) to encourage individuals to undergo screening [18], and educational initiatives to maintain medical knowledge and levels of training in relation to bowel cancer screening [19].

Intervention studies conducted to date have typically failed to demonstrate significant improvements in compliance, or have had a greater impact on some sub-groups of the population than others [20], thus increasing inequalities in screening uptake further. Many have focused on opportunistic rather than population-based screening [21], and much research has been undertaken in the US, and as such may have limited applicability to the UK context. This indicates a need to consider alternative strategies to increase the uptake of bowel cancer screening in the asymptomatic population.

The involvement of GPs has been found to improve patient compliance with bowel cancer screening [19,21,22], and the uptake of FOBt is higher in groups that are sent a reminder to participate [14,15]. Doctors are typically cited as the most trusted profession in surveys of the public [23], and healthcare professionals (GPs in particular), are consistently rated as the primary source of information that patients seek regarding health and health services [24]. This existing research points to the importance of health professionals in supporting patients in making decisions about their healthcare, yet this research has largely been conducted outside of the UK, and no studies of interventions to increase the uptake of bowel cancer screening have been conducted since the introduction of the NHSBCSP in 2006. Furthermore, non-responders to previous invitations to participate in bowel screening have not been targeted as a specific group in whom rates of screening uptake may be increased. Despite GPs having minimal direct involvement with bowel cancer screening in the programme as currently designed, a potential strategy to improve participation in the NHSBCSP is a reminder from the GP, sent to non-responders to an initial invitation to participate in bowel screening. This approach has been found to be successful in increasing attendance for breast screening [25], yet the transferability of these findings to screening for bowel cancer is unknown, as it is aimed at a different target population. Furthermore, the factors contributing to an individual's decision to participate in bowel screening are likely to differ from those affecting decisions to participate in other cancer screening programmes.

### Study aim

The main aim of this feasibility study is to evaluate the effectiveness of a primary care based intervention (GP endorsed reminder and duplicate FOBt kit) on increasing the uptake of bowel cancer screening amongst non-responders to a previous invitation to participate.

## Methods/design

This feasibility study comprises a two-armed randomised controlled trial (n = 2190 in each arm) to evaluate the effectiveness of GP endorsement and a duplicate FOBt kit (compared with no additional contact) on improving the patient uptake of FOBt screening, and an embedded qualitative study in which semi-structured interviews will be undertaken with 30 to 40 individuals in the intervention arm of the trial who return their FOBt kit following the intervention.

### The NHS Bowel Cancer Screening Programme

Bowel cancer screening in England is organised through five regional screening Hubs which invite individuals to participate in screening - each regional Hub working with up to 20 local screening centres. The Hub sends an invitation and a leaflet about bowel cancer and the screening programme to all eligible patients registered with a GP in their region, followed by a FOBt kit around eight days later. Individuals are directed to complete the FOBt at home and return it to the screening centre for analysis. Those whose FOBt shows a positive result are then invited for further investigation through colonoscopy. If the Hub does not receive a completed kit within four weeks of sending it, a reminder is sent. After 13 weeks, the 'screening episode' is closed, and those who have not returned their kit are recorded as non-responders on the Hub database. In the Midlands, bowel cancer screening is co-ordinated by the Midlands and North West Bowel Cancer Screening Hub, based in Rugby.

### Study population

The study population will be adults aged between 60 and 74, on the patient list of a general practice where the bowel screening uptake rate is < 50%, who were invited to participate in the most recent round of bowel screening but who have not returned their FOBt within the 13 week 'screening episode' recorded by the Midlands and North West Bowel Cancer Screening Hub.

### Participant selection

Participant selection will be undertaken in two stages. First, the Midlands and North West Bowel Cancer Screening Hub will identify general practices in the West Midlands where the uptake of bowel cancer screening is lower than 50%. The contact details of these practices will be obtained via the MidReC (Midlands Research Practices Consortium) database, and all eligible practices will be contacted by the research team at the University of Birmingham and invited to participate, with general practice recruitment continuing until a total of up to 30 practices have been recruited. Once practices have been recruited, the Hub will identify all eligible screening non-responders aged 60 to 74 at each participating practice. Non-responders will be defined as those who have not responded to either the initial invitation to screening, or the 4-week reminder, within a period of 13 weeks after being invited.

### Inclusion criteria

Individuals aged between 60 and 74 years old, on the patient list at a general practice with a bowel cancer screening uptake lower than 50%, who have been recorded by the screening Hub as a screening non-responder no less than one month and no more than seven months previously.

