### Sample size

General practices with a screening uptake rate of less than 50% will be purposively recruited. Assuming an average GP list size of 2,750 (information derived from the MidReC general practice database), with 11.8% of the population aged between 60 and 74 years old [26], and a bowel cancer screening participation rate of 45%, there will be 146 eligible individuals per practice (Figure 1). Thirty practices will provide 4,380 people for randomisation to the intervention or control arms of the trial. Assuming a screening uptake rate of 3.2% in the control arm (Midlands and North West Screening Hub recorded rate of delayed FOBt return amongst previous non-responders), a comparison of proportions test shows that a sample size of 934 in both the intervention and control groups is required in order to demonstrate a doubling of the uptake rate (from 3.2% to 6.4% or more) with 90% power at the 5% significance level. The larger number of patients (n = 2,190 in each group) has been chosen in order to enable sub-group analyses to be undertaken, and to account for any effects of nesting of patients within general practices should interim analyses demonstrate that such nesting is occurring.

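### The sample-size yield counts a full two-year screening round and applies no factor for the one-to-seven-month eligibility window, so 4,380 people from 30 practices is not supported as stated

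*Protocol article*

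**What the plan says.** - **Inclusion criteria** (Protocol article): the Hub must have recorded the person as a non-responder "no less than one month and no more than seven months previously".
- **Background**: "The programme aims to screen men and women aged between 60 and 74 every two years", so one round takes 24 months.
- **Sample size**: the yield rests on three inputs, "Assuming an average GP list size of 2,750", "with 11.8% of the population aged between 60 and 74 years old" and "a bowel cancer screening participation rate of 45" per cent. From these, "there will be 146 eligible individuals per practice", and "Thirty practices will provide 4,380 people for randomisation to the intervention or control arms of the trial". The same section puts the requirement for the main comparison at 934 per arm. It gives subgroup analyses and possible nesting within practices as the reasons for choosing 2,190.
- **Abstract, Methods/Design**: "Up to 30 general practices in the West Midlands with a screening uptake rate of less than 50% will be recruited". Thirty is therefore a ceiling.
- **Participant selection**: the Hub identifies eligible non-responders after practices have been recruited. The article does not say whether this is done once or repeatedly, and gives no accrual period.

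**The concern.** The eligibility rule and the yield calculation describe different groups. List size times age share times a screening rate counts people over a whole round, because each person of screening age is invited once in 24 months. The inclusion rule takes a six-month slice of that round. The sample-size section nevertheless calls the whole-round figure eligible and carries it into the trial total.

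The margin between 934 and 2,190 per arm is at stake, and possibly the 934 itself. If the window removes that margin, the subgroup analyses lose the numbers chosen for them, and the main comparison may have less than the stated 90% power. The forecasts of about 140 returned kits and 35 interviewees (Qualitative study, Feasibility) rest on 2,190 in the intervention arm and would fall with it.

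**Working it through.** **1. Reproduce the plan's figures.**

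- Yield: 2,750 x 0.118 = 324.5 people aged 60 to 74 per practice; x 0.45 = 146.0; x 30 = 4,380, or 2,190 per arm. This matches exactly and leaves no room for another factor.
- Required size for p1 = 0.032 and p2 = 0.064, two-sided 5%, 90% power: n = [1.960 x sqrt(2 x 0.048 x 0.952) + 1.282 x sqrt(0.032 x 0.968 + 0.064 x 0.936)]² / 0.032² = 936 with pooled variance under the null, or 933 unpooled. The stated 934 is reproduced.

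**2. Share of a round inside the window.** Seven minus one is 6 months. With invitations spread evenly over 24 months and one extraction per practice (both assumptions), the share is 6/24 = 25%.

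**3. Choice of pool.** The article multiplies by the participation rate of 45%, although the eligible group is non-responders. That is a separate error. Both bases are carried here: 146 per practice as printed, and 324.5 x 0.55 = 178.5.

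**4. Size and power with the window applied.** n per arm = pool x 30 x share / 2. Power = Φ{[0.032 x sqrt(n) - 1.960 x sqrt(2 x 0.048 x 0.952)] / sqrt(0.032 x 0.968 + 0.064 x 0.936)}.

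| Share of a round admitted | n per arm, 146 basis (power) | n per arm, 178.5 basis (power) |
|---|---|---|
| 20% | 438 (60%) | 535 (69%) |
| 25% | 547 (70%) | 669 (78%) |
| 33% | 730 (82%) | 892 (89%) |
| 50% | 1,095 (94%) | 1,339 (97%) |
| 100% (146 basis as in the article) | 2,190 (99.9%) | not needed |

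**5. Break-even.** The main comparison needs 2 x 934 = 1,868 people.

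- 146 basis: 1,868 / 4,380 = 42.6% of a round, or 10.2 months of closures, which is 4.2 beyond the six in the window.
- 178.5 basis: 1,868 / 5,354 = 34.9%, or 8.4 months, which is 2.4 beyond the window.
- For 4,380 people: 24 months on the 146 basis (18 further), or 4,380 / 5,354 x 24 = 19.6 months on the 178.5 basis (13.6 further).

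**6. Returns and interviews at a 25% share.** With the article's 6.4% uptake and 25% interview response, 547 x 0.064 = 35 kits and about 9 interviewees; 669 x 0.064 = 43 kits and about 11 interviewees. The article expects about 140 and 35.

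**The case against.** A reader might infer that 30 practices are bound to miss 934 per arm. The article does not support that. It does not say how a practice's list is invited over the round, and the two-year interval is given only as a programme aim. If invitations are bunched and a practice is extracted at a favourable time, well over a quarter could qualify; at 50%, power is 94-97%. Participant selection describes one identification step but does not say it happens once only. The mentions of interim analyses (Sample size) and of a monitoring committee meeting at regular intervals (Data monitoring) suggest enrolment over time, although that could be staging by practice. An accrual period is also something that a condensed article may leave to the full protocol.

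Nor does the article support saying that the interview study must fail, because recruitment to it may stop at data saturation. Falling short of 2,190 is not by itself a failure of primary power, since the stated requirement is 934. A patient number, 4,380, is already given, so a missing target is not the problem. This is also a feasibility study, from which a definitive trial would be designed and powered.

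These points limit how firmly a power figure can be stated. They do not supply the missing factor. The yield is printed and reproduces exactly without it. To reach 4,380 from one six-month window, about 82% (4,380 / 5,354) to 100% of a two-year round's non-responders would have to fall inside it, and the article gives no reason to expect that.

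**Conclusion.** The concern holds in a conditional form. It is certain that the printed yield ignores the eligibility window, so 4,380 from at most 30 practices does not follow from the inclusion rule without further conditions.

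How large the shortfall is depends on even spread of invitations and one extraction per practice. Under both, the trial would have about 547 per arm (power about 70%) on the article's own 146, or about 669 (about 78%) on the 55% basis, against 934 for 90% power. The 90% is kept only if about 35-43% or more of a round is admitted. Losses through the Exclusion criteria, fewer than 30 practices, or any allowance for clustering would lower these figures further.

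**What to change.** Apply the window share in the Sample size section and restate expected N, power, kit returns and interviews as a range over plausible shares, on a corrected pool. Reconcile Participant selection, Inclusion criteria and Sample size so that all three describe the same group. This costs only restated figures, and Trial Status says that recruitment had not begun at submission.

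Alternatively, state that the Hub repeats its extraction in the same practices as people enter the window, and for how long. With an even flow of closures, about 2.4-4.2 further months reaches 934 per arm, at the cost of repeat database extractions and a longer mailing period. Reaching 2,190 per arm would take about 14-18 further months, which is a material extension. Unless that period is planned, the subgroup-based target should be restated.

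The use of 45% where 55% is meant should be corrected as its own item. It raises the pool but, at a 25% share, does not restore 934 per arm.

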### Exclusion criteria

Patients will be excluded from the trial if:

1. They have undergone an investigation (e.g. colonoscopy) within the past two years and/or are currently under surveillance following a previous colorectal abnormality

2. They have moved outside of the 60 to 74 year age range for screening in the time since their initial 13 week screening episode

3. They have contacted the Hub requesting not to be sent any information about bowel cancer screening, or FOBt kits

### Randomisation

For each participating general practice, the Hub will separate the names and details of the screening non-responders, determine any exclusions, and send anonymised details for eligible trial participants (each individual assigned a unique identifier) to the UK Clinical Research Network (UKCRN) accredited Primary Care Clinical Research and Trials Unit (PC-CRTU) at the University of Birmingham for patients to be randomised. Randomisation will be carried out using a computer generated randomisation algorithm, with patients randomised in equal numbers to the intervention or control arms of the study (n = 4,380). Block randomisation at the general practice level will ensure a balance of the two arms within each participating practice.

### Intervention Group

Patients in the intervention arm of the trial will receive a personalised letter recommending bowel cancer screening signed by their GP and a duplicate Hema-screen FOBt kit. The letter and duplicate kit will be sent to patients on behalf of the GP by the screening Hub. The same letter template will be used for all participating GP practices, but each GP will be able to modify the wording of the letter if there are particular issues that they would like to highlight to their patients. Patients recruited to the trial will be logged by the Hub database via a reopening of the individual's screening record, which would have been closed initially after the 13 week screening window that defined that individual as a non-responder.

### Control Group

Patients randomised to the control arm of the trial will receive no additional contact (current standard practice).

### Outcome measures

The primary outcome measure will be the difference in the uptake rate of FOBt screening for bowel cancer (i.e. the proportion of individuals who return a FOBt kit to the screening Hub) between the intervention and control group after 13 weeks.

Secondary outcome measures will include sub-group analysis of screening uptake rates following the intervention, according to age, gender and deprivation quartile, and the development and validation of methods and proformas for collecting information on GP, NHSBCSP and patient costs associated with the intervention. Such costs are anticipated to include the cost to the Hub of sending GP reminders to screening non-responders; costs associated with staff workload in sending reminders; time costs for participants, and costs to primary care if the intervention results in an increased number of patients contacting their GP to discuss bowel cancer screening.

### Outcome collection

13 weeks after initial contact (i.e. when an individual's screening episode is due to close), the Hub will log the number of FOBt kits returned by individuals in the intervention and control arms of the trial, and return anonymised lists of patients, denoted by a unique identification number, to the University of Birmingham for analysis. The member of hub staff collecting the outcomes data will be blinded to randomisation group to avoid bias.

Participating general practices will be asked to record prospectively all patient consultations about bowel cancer screening during the trial. In order to determine the relative effectiveness of retrieving information on consultations where screening was discussed from routine GP records (i.e. compared to prospective recording by the GP), a retrospective analysis of routinely collected GP records will be carried out in two of the participating practices. When the trial has ended, the screening Hub will produce a list of all patients who had been randomised within these two practices. Practice staff will be asked to inform the research team of the number of consultations relating to bowel cancer screening that have been carried out for these patients.

